**Research plan**

**1. Title**

Effects of sake lees intake on fecal uremic toxins, plasma D-alanine, constipation, and gut microbiome in healthy adults: A single-arm clinical trial

**2. Outline, Purpose and Significance of the Study**

**Summary**

The efficacy of sakekasu intake on the intestinal environment in patients with chronic constipation will be evaluated in a single-arm (2-dose) intervention study. The primary endpoint will be uremic substances in stools, and secondary endpoints will be bacterial flora and short-chain fatty acids in stools.

**Objective**

The study described in this research protocol (hereafter referred to as "this study") is a pilot study aimed at evaluating changes in metabolites and bacterial flora in stools by amount and duration of sake-kasu intake in patients with chronic constipation. Based on the results obtained in this study, the amount and duration of sake lees intake in a small randomized controlled trial (RCT) in patients with chronic kidney disease (CKD) will be established.

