**3. Scientific rationale and basis for the research**

**Study summary and primary endpoints**

The subjects of this study will be patients with chronic constipation and the intervention will be consumption of 25 g/day or 50 g/day of sake-kasu. The control will be pre-intervention, and the primary endpoint will be the percentage change in the concentration of uremic substances (indole and cresol) in the stool after 2, 4, and 6 weeks. The study design will be a single-arm (2-dose) pre/post comparison.

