**Validity of the study design**

The subjects of this study shall be patients with chronic constipation without CKD. So far, there are no studies using sakekasu for CKD patients as far as we could find, and there are a few studies on patients with chronic constipation. There have been reports of an increase in certain species of bacteria that are considered beneficial bacteria after consumption of sake lees,^7)^ and the effect of improving constipation,^8)^ . Since changes in the intestinal microbiota and uremic substances can be inferred from sake lees consumption, and these changes can be expected to be observed even in those without impaired renal function, patients with chronic constipation without CKD should be included in this study.

The intervention will be intake of 25 g/day or 50 g/day of sakekasu for 6 weeks. In previous reports, studies on subjects with constipation have reported improved intestinal microbiota after 4 weeks of intake of 190 g of amazake (equivalent to 25 g of sakekasu)^7)^ and the effect of 3 weeks of intake of 50 g of sakekasu on constipation^8)^ . In addition, a study of CKD patients reported a decrease in blood uremic substance levels after 6 weeks of synbiotic supplementation^10)^ . Based on these results, the intervention in this study will be the intake of 25 g/day or 50 g/day of sake-kasu for a total of 6 weeks, and based on the results obtained, the amount and duration of sake-kasu intake in a small RCT of CKD patients will be established.

The method of outcome evaluation will be a before-and-after comparative study with no comparators. This study is conducted to obtain the rationale for setting the amount and duration of sake lees intake in a small RCT of CKD patients. Since changes in uremic substances in stools can be confirmed by pre- and post-intervention comparisons, this is a single group (2 doses) pre- and post-comparison study without a comparison group. Evaluation will be conducted 4 times at intervention, 2 weeks, 4 weeks, and 6 weeks after the intervention, and the amount and duration of intake of sake lees in a small RCT will be set.

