**Alignment with study objectives and primary endpoints**

The purpose of this study is to confirm the change of uremic substances in stool, which is the process in observing the change of uremic substances in blood by intake of sake lees for CKD patients, which is the ultimate goal of this study. There are several studies on changes in blood uremic substances using ProB and PreB supplements. For example, a study of ProB/PreB supplementation and its effect on blood uremic substances (p-cresyl sulfate) in patients with CKD stages 3 to 4 reported a significant decrease in p-cresyl sulfate after 2 and 4 weeks.^6)^ A similar study in non-dialysis patients with CKD stages 4 to 5 also showed a decrease in p-cresyl sulfate after 6 weeks.^10)^ These results favor a mechanism by which ProB/PreB altered the gut microbiota and gut metabolites, thereby reducing uremic substances in the blood. To elucidate this mechanism, it is necessary to confirm the uremic substances in stools after intake of sake lees, and the purpose of this study can be achieved by evaluating the primary endpoints. In healthy subjects with normal renal function, blood uremic substances are not evaluated in this study because no change in blood uremic substances is expected to occur before and after intake of sake lees.

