**6. Research methods**

**(1) Study design**

Single arm (2 doses) before/after study (single center)

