**Research Procedures**

1. Provide nutritional guidance prior to intervention using our own sake-kasu recipe (Attachment 1).
2. Sake lees 25 g/day or sake lees 50 g/day for 6 weeks
3. Sakekasu (sake lees) from "Kakuma-no-sato", a refined sake sold by Kanazawa University, will be used. The same lot of sakekasu will be provided to the participants free of charge in order to ensure the same conditions for the intervention.
4. Store sake lees in a refrigerator at about 5℃.
5. Participants can choose how to cook sake-kasu from a collection of sake-kasu recipes
6. Outcome items will be assessed at intervention, 2, 4, and 6 weeks
7. The intake of sake lees and defecation should be recorded daily on the record sheet.
8. The timing and frequency of sakekasu intake is not set. For example, 25 g of sakekasu can be consumed in one meal or divided into three meals.
9. During the introduction period (2 weeks) and the intervention period (6 weeks), the consumption of lactic acid bacteria preparations, foods for specified health uses and foods with functional claims that improve the intestinal environment is prohibited. (Fermented foods other than sake lees, such as miso and yogurt (general foods), may be consumed.
10. The same dinner (a frozen home-delivered lunch with controlled nutritional value) on the day before the evaluation
11. Breakfast on the day of evaluation after 2, 4, and 6 weeks will be the same meal containing sakekasu

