**Data Analysis Method**

The primary endpoint, the concentration of uremic substances in the stool, will be analyzed before and after the intervention using analysis of variance and Dunnett test, two-tailed, at a 5% level of significance.

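### The study is meant to inform how much and how long in the later CKD trial, but the stated before/after analysis names no comparison between doses or between post-baseline visits

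*Protocol*

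**What the plan says.** **Purpose.** The Objective in section 2 gives the aim as "evaluating changes in metabolites and bacterial flora in stools by amount and duration of sake-kasu intake in patients with chronic constipation" and says the results will settle both for a small RCT in CKD. The end of the Background repeats this. Under Validity of the study design (section 3) the protocol adds: "This study is conducted to obtain the rationale for setting the amount and duration of sake lees intake in a small RCT of CKD patients". Under Alignment with study objectives and primary endpoints it gives a further aim: "The purpose of this study is to confirm the change of uremic substances in stool".

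**Intervention and visits.** Research Procedures (section 6) specifies "Sake lees 25 g/day or sake lees 50 g/day for 6 weeks", with assessments at baseline and at weeks 2, 4 and 6.

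**Analysis.** The study summary in section 3 states: "The control will be pre-intervention, and the primary endpoint will be the percentage change in the concentration of uremic substances". Data Analysis Method (section 6) says that the stool concentration "will be analyzed before and after the intervention using analysis of variance and Dunnett test", two-tailed at 5%. Validity of the study design says "this is a single group (2 doses) pre- and post-comparison study without a comparison group", and section 6(1) labels the design in the same way.

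**Allocation and size.** The principal investigator assigns participants in numerical order, and no ratio is given. Section 10 sets the total at eight on grounds of feasibility.

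**The concern.** Choosing an amount needs an estimate of how 50 g differs from 25 g. Choosing a duration needs an estimate of what week 4 adds to week 2, and week 6 to week 4. Dunnett's procedure compares several levels with one control. With pre-intervention as that control, it gives weeks 2, 4 and 6 against baseline and nothing else. The statement that there is no comparison group points the same way, although two doses run side by side.

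At stake is the main product of the pilot. The amount and duration carried into the CKD trial would have no planned estimate of either difference behind them, and whoever designs that trial would have to improvise one from before/after results.

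**Working it through.** **1. Is there a figure to reproduce?** No. Section 10 gives eight participants with no effect size, SD or power. The check is therefore mainly a comparison of questions with contrasts.

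**2. Questions against stated contrasts**

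| Question set by the protocol | Contrast needed | Named in the analysis? |
|---|---|---|
| Do stool uremic substances change? | Each visit vs baseline | Yes |
| When is a change detectable? | Each visit vs baseline | Yes |
| Does the amount matter? | 50 g vs 25 g, by visit | No |
| Does longer intake add anything? | Week 4 vs 2, week 6 vs 4 | No |

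That baseline is Dunnett's reference is an inference from the study summary; Data Analysis Method does not name it. It also does not list the ANOVA factors or say whether the doses are pooled, so both readings are examined below.

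**3. If doses are pooled.** With 4 per dose (assumed), the pooled mean change is (4 × change at 25 g + 4 × change at 50 g) / 8.

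| Mean change, 25 g | Mean change, 50 g | Pooled |
|---|---|---|
| −30% | −30% | −30% |
| −60% | 0% | −30% |
| 0% | −60% | −30% |

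Three different dose patterns give the same result, so the amount is not identified.

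**4. If each dose is tested separately.** Take a simple paired t-test with n = 4, two-sided 5%, without multiplicity adjustment. 80% power needs a mean change of about 2.13 SD (with all 8 pooled, about 1.16 SD). Suppose both doses truly have that same 2.13 SD change. The chance that exactly one of the two tests is significant is 2 × 0.8 × 0.2 = 0.32. A split verdict would arise about one time in three with no dose difference at all, so separate tests do not stand in for the contrast.

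**5. Duration.** Research Procedures gives everyone six weeks, so duration can be judged only across visits within person. (The allocation paragraph speaks of assigning duration as well; the two places should be reconciled.) Visit-versus-baseline tests show when a change becomes detectable. Subtracting two of them gives a point difference between visits, but not its interval, and no such contrast is named.

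**6. What a dose contrast would deliver.** The model is a two-group comparison of change at one visit, in units of the SD of the change, because no SD is given. Degrees of freedom are 8 − 2 = 6.

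Half-width of the 95% CI = t(0.975, 6) × √(1/n₁ + 1/n₂)

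- 4:4 split: 2.447 × √(1/4 + 1/4) = 2.447 × 0.707 = 1.73 SD
- 5:3 split: 2.447 × √(1/5 + 1/3) = 2.447 × 0.730 = 1.79 SD
- 6:2 split: 2.447 × √(1/6 + 1/2) = 2.447 × 0.816 = 2.00 SD

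Power at 4:4 (noncentral t, 6 df, noncentrality d × √(4/2)):

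| True difference | Power |
|---|---|
| 0.5 SD | 9% |
| 1.0 SD | 22% |
| 1.5 SD | 43% |
| 2.0 SD | 66% |
| 2.38 SD | 80% |

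The contrast is worth having as an estimate. It cannot serve as a test.

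**The case against.** The best defence has four parts.

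- **The before/after analysis answers a stated question.** This stands. Confirming a change in stool uremic substances is an aim in its own right, and the planned comparisons address it. A reader might infer that setting amount and duration is the sole purpose and that the analysis fails the trial altogether; the Alignment section rules that out.
- **A dose factor is unstated, not excluded.** This also stands. An ANOVA can carry dose or be run within dose, the design label mentions two doses throughout, and a statistical analysis plan, not at hand here, could supply the terms. A reader might infer that the protocol pools the doses; it does not say so. But the protocol does more than leave detail open. It names the test and the control and says there is no comparison group. A later plan that followed those statements would contain no dose contrast, and one that added it would depart from them.
- **No significance rule for choosing the dose is stated.** Correct. The 5% level applies to the before/after change, and the protocol says only that the choice will follow from the results. A reader might infer that the choice will be made by p-values; the text does not support that. It gives no basis for the choice at all.
- **With eight people in a feasibility pilot, and allocation in numerical order, a dose contrast settles little.** True. It argues for reporting the contrast descriptively with its interval, not for leaving it out.

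**Conclusion.** The point holds as a mismatch between a main stated purpose and the only stated analysis. The analysis provides change from baseline and its timing. It provides no interval estimate of the 50 g versus 25 g difference or of the gain from longer intake, whether the doses are pooled or tested separately. The gap is complete for amount and partial for duration, since visit-versus-baseline results do carry some information on timing.

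Repairing it would not make the dose choice conclusive. Under an assumed 4:4 split, with SD meaning the SD of the change and no dropout, the 95% interval is about ±1.73 SD (up to ±2.00 SD at 6:2), and 80% power requires a difference of about 2.4 SD. Because allocation is by the investigator in numerical order and not described as random, the contrast is also open to imbalance between the groups.

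The conclusion rests on reading pre-intervention as Dunnett's reference, which the study summary supports.

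**What to change.** 1. In Data Analysis Method, replace or supplement ANOVA and Dunnett with a repeated-measures (mixed) model of log concentration, fitted for each substance, with dose, visit, dose-by-visit and baseline log concentration. Eight people at three post-baseline visits give 8 × 3 = 24 observations for six dose-by-visit means and a baseline slope, so keep the covariance structure simple.
2. Report, with 95% CIs: change from baseline within each dose; the 50 g/25 g ratio at weeks 2, 4 and 6; and the week 4 vs 2 and week 6 vs 4 contrasts. A ratio r converts to a percentage change as 100 × (r − 1), which keeps the link with the primary endpoint.
3. State that amount and duration will be judged from these estimates together with adherence, and not from significance. Call the dose contrast descriptive, with small numbers and the allocation method as the reasons.
4. In Validity of the study design and section 6(1), describe two dose groups, each compared with its own baseline.

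**Cost.** No extra participants, visits or samples. It is a small change of analysis method and not only of wording, and the wide intervals for the dose difference will be visible.

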**Background**

Patients with CKD are known to have dysbiosis (DysB), a condition in which the intestinal microbiota is disrupted^1)^ . DysB occurs in CKD patients due to elevated urea and uric acid in the blood that migrate into the intestinal tract, medication, and dietary fiber deficiency due to dietary restriction. These decrease beneficial strains that produce short-chain fatty acids, which are a source of energy for the intestinal epithelium and involved in intestinal immune regulation^2)^ , and conversely increase harmful strains that produce uremic substances such as indoles and cresols^3)^ . In other words, the metabolites produced by DysB are altered, and a vicious cycle may be formed in which CKD develops^4)^ . For example, deficiency of short-chain fatty acids causes weakening of the intestinal epithelial barrier, and pathogens and uremic substances that should normally remain in the intestinal tract may pass through the intestinal epithelium and enter the bloodstream, leading to renal damage via chronic inflammation and other factors.^5)^

This makes regulation of the gut microbiota and metabolites in CKD patients important in the prevention of CKD progression. Therefore, factors involved in the regulation of gut microbiota and metabolites need to be clarified.

Diet is a factor involved in the gut microbiota and metabolites, and the common treatment of DysB is a probiotic (intake of beneficial bacteria, ProB) and prebiotic (intake of dietary fiber, PreB) diet, with ProB and PreB being tested in patients with CKD. ProB and PreB are being tested in CKD patients. For example, ProB/PreB in CKD patients has been reported to decrease blood levels of uremic substances (p-cresyl sulfate).^6)^ Thus, ProB/PreB suitable for CKD patients may be a useful DysB treatment.

Sake lees contains beneficial bacteria and dietary fiber, and has both ProB and PreB functions suitable for CKD patients. In addition, it contains low amounts of phosphorus and potassium, which are restricted in CKD patients, and low amounts of salt. As for its effects, studies on people with constipation have reported that consumption of 190 g of amazake (equivalent to 25 g of sakekasu) for 4 weeks improves the intestinal microflora^7)^ and 50 g of sakekasu for 3 weeks improves constipation^8)^ .

D-serine and D-alanine, a type of D-amino acid, have been confirmed to have renoprotective effects by research members^9)^ . Fermented foods such as sake-kasu contain D-amino acids, and direct intake of D-amino acids from sake-kasu may provide renoprotective effects. However, there are no studies that have examined changes in D-serine and D-alanine in stool and blood due to intake of sakekasu. In addition, there are no studies on changes in stool flora related to metabolites such as uremic substances and short-chain fatty acids among the previously reported studies on sake-kasu intake and stool flora, and there is a lack of data on evaluation indices to show the usefulness of sake-kasu intake.

Therefore, the purpose of this study is to evaluate changes in metabolites and bacterial flora in stools by amount and duration of sake-kasu intake in patients with chronic constipation without CKD. Based on the results obtained in this study, we will establish the amount and duration of sake lees intake in a small RCT of patients with CKD.

**3. Scientific rationale and basis for the research**

**Study summary and primary endpoints**

The subjects of this study will be patients with chronic constipation and the intervention will be consumption of 25 g/day or 50 g/day of sake-kasu. The control will be pre-intervention, and the primary endpoint will be the percentage change in the concentration of uremic substances (indole and cresol) in the stool after 2, 4, and 6 weeks. The study design will be a single-arm (2-dose) pre/post comparison.

**Validity of the study design**

The subjects of this study shall be patients with chronic constipation without CKD. So far, there are no studies using sakekasu for CKD patients as far as we could find, and there are a few studies on patients with chronic constipation. There have been reports of an increase in certain species of bacteria that are considered beneficial bacteria after consumption of sake lees,^7)^ and the effect of improving constipation,^8)^ . Since changes in the intestinal microbiota and uremic substances can be inferred from sake lees consumption, and these changes can be expected to be observed even in those without impaired renal function, patients with chronic constipation without CKD should be included in this study.

The intervention will be intake of 25 g/day or 50 g/day of sakekasu for 6 weeks. In previous reports, studies on subjects with constipation have reported improved intestinal microbiota after 4 weeks of intake of 190 g of amazake (equivalent to 25 g of sakekasu)^7)^ and the effect of 3 weeks of intake of 50 g of sakekasu on constipation^8)^ . In addition, a study of CKD patients reported a decrease in blood uremic substance levels after 6 weeks of synbiotic supplementation^10)^ . Based on these results, the intervention in this study will be the intake of 25 g/day or 50 g/day of sake-kasu for a total of 6 weeks, and based on the results obtained, the amount and duration of sake-kasu intake in a small RCT of CKD patients will be established.

The method of outcome evaluation will be a before-and-after comparative study with no comparators. This study is conducted to obtain the rationale for setting the amount and duration of sake lees intake in a small RCT of CKD patients. Since changes in uremic substances in stools can be confirmed by pre- and post-intervention comparisons, this is a single group (2 doses) pre- and post-comparison study without a comparison group. Evaluation will be conducted 4 times at intervention, 2 weeks, 4 weeks, and 6 weeks after the intervention, and the amount and duration of intake of sake lees in a small RCT will be set.

**Alignment with study objectives and primary endpoints**

The purpose of this study is to confirm the change of uremic substances in stool, which is the process in observing the change of uremic substances in blood by intake of sake lees for CKD patients, which is the ultimate goal of this study. There are several studies on changes in blood uremic substances using ProB and PreB supplements. For example, a study of ProB/PreB supplementation and its effect on blood uremic substances (p-cresyl sulfate) in patients with CKD stages 3 to 4 reported a significant decrease in p-cresyl sulfate after 2 and 4 weeks.^6)^ A similar study in non-dialysis patients with CKD stages 4 to 5 also showed a decrease in p-cresyl sulfate after 6 weeks.^10)^ These results favor a mechanism by which ProB/PreB altered the gut microbiota and gut metabolites, thereby reducing uremic substances in the blood. To elucidate this mechanism, it is necessary to confirm the uremic substances in stools after intake of sake lees, and the purpose of this study can be achieved by evaluating the primary endpoints. In healthy subjects with normal renal function, blood uremic substances are not evaluated in this study because no change in blood uremic substances is expected to occur before and after intake of sake lees.

**4. Research Subjects and Selection Policy**

**(1) Eligibility criteria**

1. Healthy subjects who meet the diagnostic criteria^11)^ for constipation from the date of approval through January 2022

1. diagnostic criteria for constipation

Satisfy at least two of the following six criteria

1. Strong straining is required for more than one-fourth of bowel movements.
2. More than one-fourth of defecations are fecal or hard (type 1 or 2 on the Bristol stool shape scale).
3. More than one-fourth of the time, the patient feels a sensation of residual stools.
4. More than one-quarter of defecations are accompanied by a sensation of rectal obstruction or dyspareunia.
5. Manual assistance is required for more than one-fourth of bowel movements (e.g., stool removal, perineal compression, etc.).
6. Spontaneous defecation frequency is less than 3 times per week.

2. diagnostic criteria for "chronic

Symptoms present for at least 6 months and meeting the above criteria for the last 3 months

1. Persons who give written consent to participate in this study
2. Persons who are 20 years of age or older at the time of obtaining consent

